From the call made by experts to design strategies contextualized to the local reality of active transportation to school [75,76] to increase physical activity levels and improve the physical and mental health of children, the project “Moving to School” (MOV-ES) was born. This project will be carried out during the period 2024–2026 in a city in Southern Chile that has urban characteristics below the national average in terms of population density (949.8 inhabitants/km^2^), sports facilities (0.81 m^2^/inhabitant), green areas (6.40 m^2^/inhabitant), and pollution problems above the national average [77]. Therefore, the aim of this study protocol for the MOV-ES project is to determine the effect of an active transport educational program based on the ecological model on the physical and mental health of high school students. Given the evidence from previous studies focused on reducing physical inactivity, it is hypothesized that (i) the MOV-ES intervention will result in a 3% decrease in mean percent body fat in the experimental group compared to the control group, and (ii) the MOV-ES intervention will result in a significant increase in executive function (inhibition, cognitive flexibility, and working memory), physical fitness (aerobic capacity and muscle strength), and mental health (mood disorders, cognitive functioning) in high school students.

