### 2.3. Sample Size Calculation

While feasibility trial results typically inform sample size calculations for scalability cluster randomized trials, an approximate sample size estimate is required for budgeting this large-scale trial. The sample size was determined to be 3 clusters (classrooms) per condition (n = 6 clusters) using the GRT sample size calculator from the NIH (researchmethodsresources.nih.gov). This calculation considered an absolute difference of 3% (alpha error of 0.05 and statistical power of 0.80) between the experimental group (EG) and control group (CG) in mean body fat percentage (with a standard deviation of 5), an average of 30 participants in each cluster, and a variance inflation factor of 1.05 based on prior research findings. Following the feasibility study and informed by qualitative research insights, adjustments will be made to refine the MOV-ES intervention.

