Physical fitness: It will be assessed with the application of different tests validated in the school population, with high reliability and ease of application. The order of application of the tests contemplated is: (i) A 20 m shuttle run test will be used to measure the maximal oxygen consumption (VO_2_ max). This test allows a very reliable and easy-to-use evaluation. This is a maximal test involving a continuous run between two lines separated by 20 m at the same time as the beeps are recorded [84]. The athlete’s score is the level and number of laps (20 m) achieved before he/she could not keep up with the recording. (ii) A long jump test with feet together will be used to measure lower body muscle strength [85]. This test allows for or assesses the explosive force (power) of the extensor muscles of the legs; the number of centimeters advanced, from the jump line to the edge closest to the jump line, of the foot that was farthest behind after the fall is recorded. (iii) The upper body muscle strength will be assessed with the hydraulic dynamometer (Camry, model EH101, Zhongshan, China), which allows evaluation of great reliability and easy application [86].

Mental well-being: This will be measured with the Depression, Anxiety, and Stress Scale (DASS-21). Is an instrument designed to assess the negative emotional states of depression, anxiety, and stress [87,88]. The depression subscale is formed by questions 3, 5, 10, 13, 16, 17, and 21. Questions 2, 4, 7, 9, 15, 19, and 20 formed the anxiety subscale. The stress subscale was formed by questions 1, 6, 8, 11, 12, 14, and 18. The total scores categorize each subscale into three levels: mild, moderate, and severe. Finally, participants will be classified as no risk (<6) or risk (>6).

Academic achievement: To assess this variable, the grades of all subjects from the first academic semester will be considered and compared with those of the second semester (intervention). The rating scale in Chile is from 1 to 7, with 7 being the maximum rating.

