#### 2.8.1. Intention-to-Treat Analysis

The statistical analysis plan is outlined as follows: Following verification of the effectiveness of randomization, mixed regression models will be employed, with each outcome variable serving as the dependent variable and interventions treated as fixed effects (1 = EG and 0 = CG). Models will be adjusted for baseline values, age, and classroom. Absolute differences in variable changes between baseline and final measurements will be reported as results. For dichotomous dependent variables, odds ratios will be calculated. Sensitivity analyses will involve multiple imputation techniques to address missing measurement values. Five databases will be imputed and analyzed in parallel. In the event of imbalances threatening group comparability, propensity scores will be utilized to control for covariate imbalances. Analyses will be conducted from an intention-to-treat perspective, where subjects remain in the analysis group (EG or CG) to which they were originally assigned, regardless of their intervention compliance. The results will be considered statistically significant at *p* < 0.05.

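### The DASS-21 outcome ends in a risk / no risk cut, and the plan does not say that the subscale scores are what will be analysed; if the class is tested, information is lost needlessly

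*Protocol article*

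**What the plan says.** Protocol article, section 2.7.2 (Mental well-being), assigns seven DASS-21 items to each of three subscales: depression, anxiety and stress. It then sorts each subscale into three severity levels and ends: "Finally, participants will be classified as no risk (<6) or risk (>6".

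Section 2.8.1 makes each outcome variable the dependent variable of a mixed regression model adjusted for baseline, age and classroom, and reports absolute differences in change. It adds: "For dichotomous dependent variables, odds ratios will be calculated". It does not mention the DASS-21.

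Hypothesis (ii) in the Introduction predicts a significant improvement in several domains. Mental health, including mood disorders, is one of them, with no effect size given. Section 2.7.2 lists mental well-being as a secondary outcome, and the only sample size calculation (section 2.3) is for body fat percentage.

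**The concern.** A sum of seven items is an ordered score with many values. The text reduces it to three levels and then to two classes, and the two-class form comes last. No other outcome in section 2.7 is explicitly cut in two, so the odds-ratio sentence in section 2.8.1 fits the DASS-21 class most naturally.

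On that reading, a student who moves from severe to just above the cut counts as unchanged, as does one who improves within the lower class. Only crossings of the cut carry information. The trial has six classrooms and little precision to spare, so a real shift in mood would be easier to miss, and a null odds ratio could be mistaken for absence of a mental health effect. The protocol gives no reason for preferring the class to the score.

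**Working it through.** **Inputs from section 2.3 (stated for body fat only).** "This calculation considered an absolute difference of 3" percentage points, "with a standard deviation of 5", "an average of 30 participants in each cluster", "a variance inflation factor of 1.05 based on prior research findings", and "alpha error of 0.05 and statistical power of 0.80". There are 3 classrooms per condition, so 90 students per arm. Sidedness is not stated; I take two-sided.

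**Step 1: reproduce the plan's figure.** Required n per arm = 2 × SD² × VIF × (t₀.₉₇₅ + t₀.₈₀)² / Δ², with df = 2(3 − 1) = 4:

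2 × 25 × 1.05 × (2.776 + 0.941)² / 9 = 80.6 per arm, and 80.6 / 30 = 2.69 clusters, rounded up to 3.

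The stated 3 clusters per condition reproduce, and 4 df is the right reference for what follows.

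**Step 2: power of the full score.** For a standardised effect d, the noncentrality is d / √(2 × 1.05 / 90) = d / 0.1528, referred to a noncentral t with 4 df. For d = 3/5 = 0.6 it is 3.93, giving 83% power.

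**Step 3: power of the two-class outcome.** Assume a normal score cut where a share p₀ of controls is at risk. The intervention share is p₁ = Φ(z(p₀) − d), with standard error √[(p₀(1 − p₀) + p₁(1 − p₁)) × 1.05 / 90], again with 4 df.

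Worked case, d = 0.6 and p₀ = 0.30:
- p₁ = Φ(−0.524 − 0.6) = 0.130
- difference = 0.170
- standard error = √[(0.210 + 0.113) × 1.05 / 90] = 0.0614
- noncentrality = 2.76, power 55%, so a loss of 28 points

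**Step 4: range over assumptions.** The documents give no DASS-21 effect, SD or risk share, so both d and p₀ (20% to 60%) are assumed:

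| Effect (SD) | Power, score | Power, two classes | Loss (points) |
|---|---|---|---|
| 0.1 | 7% | 5–6% | 1 to 2 |
| 0.2 | 17% | 10–13% | 5 to 7 |
| 0.3 | 33% | 17–23% | 10 to 15 |
| 0.4 | 51% | 26–36% | 15 to 25 |
| 0.6 | 83% | 46–67% | 16 to 38 |
| 1.0 | over 99% | 75–97% | 2 to 24 |

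The loss is largest at the 20% risk share. If only 10% of controls were at risk, it would be 53 points at 0.6 SD.

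These figures carry the body-fat inflation factor over to the DASS-21, treat the score as normal, and leave baseline adjustment out of both analyses. Real subscale scores are integers and may be skewed, so the figures show the order of the loss and are not predictions.

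**The case against.** The strongest objection is that the protocol never says the class is tested. Section 2.7.2 describes how the instrument is scored, and a scoring description can list scores, levels and a class without choosing among them. The default in section 2.8.1, a baseline-adjusted model reporting absolute differences in change, suits a score. The odds-ratio sentence is generic and could serve another yes/no variable, for example one from the active transportation questionnaire. The choice of analysed form might also be left to a statistical analysis plan. This stands in part: a reader might infer that the protocol fixes the risk class as the test of the mental health hypothesis, and the text does not go that far. The loss is conditional on that reading. What survives is that the article itself writes down the cut and the binary effect measure, in that order, and nothing gives the scores precedence.

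Second, the size is not in the documents. The 0.6 SD effect and the factor 1.05 belong to body fat. A reader might take the 0.6 SD row as this trial's loss; that is not supported. At 0.1 to 0.2 SD the cut costs only about 1 to 7 points, and the full score would probably miss the effect as well. This objection stands, so only a range under stated assumptions is given.

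Third, the outcome is secondary and was not sized, so no stated power is contradicted. KIDSCREEN-27, with no cut stated, also bears on psychological well-being. Both points hold and limit the weight of the concern.

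Finally, a score of exactly 6 falls in neither class, and the text does not say whether the cut applies to each subscale or to the total. That is a separate defect in the same sentence; repairing it would not restore the information lost by cutting.

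**Conclusion.** The concern holds in conditional form. The last form given to the DASS-21 outcome is a two-class cut, odds ratios are planned for dichotomous variables, and the scores are not named as the analysed form. If the class tests the mood-disorder part of hypothesis (ii), the cut lowered power in every scenario tabulated. For effects of 0.2 to 0.6 SD and 20% to 60% of controls at risk, the loss is about 5 to 38 points, depending on an effect size and a risk share that the documents do not supply. The range does not bound the loss: it is smaller for very small effects, can be smaller for very large ones, and is larger when few students are at risk.

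This is an avoidable loss of information on a secondary outcome. It is not an error in the sample size or a contradiction of any stated power. It should be changed because the better analysis uses data already collected.

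**What to change.** In section 2.7.2, state that the three DASS-21 subscale scores at final measurement are the analysed mental well-being outcomes. In section 2.8.1, state that they are analysed on their full scale in the same mixed model as the other continuous outcomes, with the baseline subscale score as covariate, and with an ordinal or rank-based model if the scores are strongly skewed. Say that severity levels and the risk class are descriptive, or at most a supporting odds ratio that does not decide the hypothesis. If the class is reported, define where a score of 6 falls and which scale the cut applies to.

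The cost is about one sentence in each section. The item responses are already collected and summed, so no new data, participants or staff are needed. The small downside is that a mean score difference is less direct to explain than a risk share, which can still be reported alongside.

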### 2.6. Intervention

The CG will participate in the initial and final measurements but will not receive any intervention, attending their traditional physical education classes. On the other hand, the EG (MOV-ES) will receive an educational intervention within their physical education class. The contents of this intervention involve intrapersonal (benefits of active transportation and safety on the way to school), interpersonal (family safety), organizational, community, physical-environmental, and political (safety, infrastructure, and quality) factors [79]. The program will comprise a weekly session lasting 60 to 90 min each, spanning a total of 16 weeks. The entire intervention program was conducted during school hours within the framework of physical education classes and hosted on the premises of each respective institution. The curriculum will be structured into didactic units, which are divided into 16 subtopics that will be addressed in each of the sessions. Each session will have the following structure: (i) audiovisual presentation; (ii) application of content; and (iii) practical work. The contents will be complemented by the presentation of graphic and audiovisual materials together with practical components in the school space.The contents will follow the recommendations for active transportation interventions in schoolchildren [75] and the material available from the PACO Project (http://profith.ugr.es/pages/investigacion/recursos/manualbici, accessed on 20 June 2024). A summary of the progression and unit structure of the MOV-ES interventions is presented in Table 1.

The sessions of the last month of intervention will include practical activities in bicycle mechanics and walking in the school environment (outside the school). Depending on the possibilities of each school, cycling sessions will be included. At the end of the intervention, and to motivate students to engage in active transportation, both EG and CG participants will receive educational infographics.

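### Academic achievement counts all subjects and does not exclude physical education, the one class whose content differs by arm in the second semester

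*Protocol article*

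**What the plan says.** Academic achievement is a secondary outcome. Section 2.7.2 of the protocol article sets its content: "the grades of all subjects from the first academic semester will be considered and compared with those of the second semester (intervention". It adds the scale: "The rating scale in Chile is from 1 to 7, with 7 being the maximum rating". No subject is excepted.

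Section 2.6 says where the programme is taught: "the EG (MOV-ES) will receive an educational intervention within their physical education class". Its extent is also given: "The program will comprise a weekly session lasting 60 to 90 min each, spanning a total of 16 weeks". Of the control group, the same section says that it "will not receive any intervention, attending their traditional physical education classes". Table 1 places weeks 1 to 8 of the programme in the classroom, weeks 9 to 12 inside the school and weeks 13 to 16 outside it.

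The analysis in Section 2.8.1 is a mixed regression model for each outcome: "Models will be adjusted for baseline values, age, and classroom".

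**The concern.** The trial changes what is taught in one school subject, and that subject is not excluded from an outcome meant to show whether achievement improves. The Introduction cites improved academic achievement as a benefit of active transportation, that is, as something that follows from a change in how students travel. A physical education grade earned partly on the programme's own units is a different quantity. It can move because the material is different or is marked differently.

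What is at stake is the interpretation of one secondary outcome. An estimated difference in grades, in favour of either arm, could come in part from physical education alone and be read as a general academic effect. Neither primary outcome is touched, and nor is the sample size.

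**Working it through.** **1. The plan's own figure.** The only sample-size calculation, in Section 2.3, is for body fat: "an absolute difference of 3% (alpha error of 0.05 and statistical power of 0.80", "in mean body fat percentage (with a standard deviation of 5", 30 students per classroom and a variance inflation factor of 1.05.
- Normal approximation: 44 per arm; 44 × 1.05 = 46.2; 46.2 / 30 = 1.54 classrooms.
- With t quantiles on 2(g − 1) degrees of freedom for g classrooms per arm, g = 2 would need 5.59 classrooms, so two are too few. At g = 3 the need is 80.6 students, and 80.6 / 30 = 2.69 classrooms, so three suffice (power about 0.83 to 0.84).

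The stated three classrooms per condition is reproduced. It has no bearing on this point, and the article states no target difference for grades.

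**2. The two semesters side by side.**

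| | First semester (baseline) | Second semester (intervention) |
|---|---|---|
| Experimental group, physical education | before the programme | programme taught within the class |
| Control group, physical education | usual | usual |
| Other subjects, both arms | usual | usual |

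By design, the arms differ in what they are taught in one cell only: physical education in the second semester.

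**3. Whether the planned model removes it.**
- Baseline grades come from before the content diverges, so they carry no information on the later difference.
- Age is unrelated to it.
- Each classroom belongs to one arm. A classroom term can describe variation between classes within an arm, but it cannot separate a feature shared by all classes of an arm from the arm effect itself.
- Multiple imputation deals with missing values and propensity scores with covariate imbalance. Neither addresses this.

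**4. Size, if grades are pooled with equal weight.** Let d be the difference between arms in the physical education grade alone and k the number of subjects. The shift in the mean is d/k. The article gives neither, so both are assumed: d = 0.2 to 1.0 points, k = 8 to 12.

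| d | k = 8 | k = 10 | k = 12 |
|---|---|---|---|
| 0.2 | 0.025 | 0.020 | 0.017 |
| 0.5 | 0.062 | 0.050 | 0.042 |
| 1.0 | 0.125 | 0.100 | 0.083 |

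The range is 0.017 to 0.125 grade points. With physical education left out, this shift is 0.

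**5. Comparison with what the trial could detect.** Take 90 students per arm, the inflation factor of 1.05 borrowed from body fat, and 4 degrees of freedom. The smallest difference detectable with 80% power is (t0.975 + t0.80) × SD × √(2 × 1.05 / 90). For an assumed between-student SD of 0.4, 0.6 and 0.8 this gives 0.227, 0.341 and 0.454 points. The largest shift in step 4 lies below all three. This calculation ignores baseline adjustment, which would lower the detectable difference, and stronger clustering of grades, which would raise it.

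**The case against.** The strongest reply is that the article does not say enough for a bias to be shown. It says that grades are considered and compared. It does not say that they are averaged, and a subject-by-subject comparison would show physical education on its own and leave the other subjects clean. It does not say how physical education is graded in either arm, or whether programme sessions count towards that grade. Different content need not produce different grades. Overall grades across all subjects are also a legitimate measure of school performance, and how they are combined is a detail that an article may leave to the full protocol.

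Most of this stands, and it limits the point. A reader might infer three stronger things that the documents do not support:
- That the outcome is an average which will carry a spurious difference. Pooling is not stated, and a difference is possible but not established.
- That staff who know the allocation give the physical education grade. Section 2.1 calls the trial double blind. Whoever teaches the class must know whether it contains the programme, but the article does not say who teaches or marks it.
- That the bias runs in one direction. Nothing in the documents fixes its sign.

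What the reply does not remove is the stated rule. The article chooses all subjects, and one of them is altered by design in one arm. Even for a reader who counts physical education as achievement, its second-semester grade is not like for like between the arms. If subjects are compared separately, the problem is confined to the physical education comparison.

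**Conclusion.** The point holds as a minor weakness in how a secondary outcome is defined. The definition includes, or at least does not exclude, the subject in which the intervention is taught, and the planned adjustment cannot separate a content or marking difference from an effect on achievement. This presumes that physical education is graded and enters the outcome, as the all-subjects rule implies but does not spell out.

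On the assumed inputs and equal weighting the effect is about 0.02 to 0.13 grade points. That is unlikely to produce a significant result by itself, but it would add to or subtract from any estimate. It is no ground for calling the academic result invalid.

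**What to change.** Define academic achievement as the grades of all subjects except physical education, in both semesters, and report the physical education grade separately by arm. At minimum, keep the present definition and prespecify the analysis without physical education as a sensitivity analysis. In either case, state whether subjects are pooled and with what weights.

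The cost is a sentence or two in Section 2.7.2. The grades of all subjects are already to be obtained, so no data collection, sample size or power figure changes. The small downside of the first option is that the main measure no longer equals the overall school grade that families and schools know; the sensitivity-analysis option avoids this.

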### 2.5. Participants

All first-year high school students (approximately aged 15 to 16 years old) from the chosen schools will be invited to participate in this study. Inclusion criteria for the students entail: (i) enrollment in the designated school; (ii) parental or legal guardian authorization (consent); (iii) do not have any motor problems to perform autonomous transport; and (iv) voluntary agreement from the students to take part in the study (assent).

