#### 2.7.1. Primary Outcomes

The primary variables and the selected instruments for their measurement are summarized in Table 2. In addition to sociodemographic variables (such as birth date and gender), the following information will be collected from each participant at baseline:

Body composition: The percentage of fat mass and fat-free mass will be obtained using eight electrodes of tetrapolar bioimpedance (InBody 570^®^, Body Composition Analyzers, Seoul, Republic of Korea). Prior to the assessments, students will be asked to come to the measurement in light clothing, without metal-containing garments, and with the possibility of removing their footwear. This whole process will be carried out under the supervision of a school teacher.

Executive function: The NIH Toolbox for Assessment of Neurological and Behavioral Function^®^ (NIH Toolbox^®^ in Spanish, v. 1.8) was created as a comprehensive set of neurobehavioral assessments intended to rapidly evaluate sensory, motor, emotional, and cognitive abilities throughout the lifespan, spanning ages 3 to 85 years, available in both English and Spanish [80]. Inhibitory control and attention will be measured using the Flaker Test of Attention and Inhibitory Control. Cognitive flexibility and attention will be measured using the Dimensional Change Card Sorting Test, and working memory will be measured using the List Sorting Working Memory Test. For each test, the evaluator will read the specific instructions of the test to be applied, making sure, by verbal confirmation, that the subject understands the procedure. The results of the tests are extracted by means of scores.

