School questionnaire: Based on the questionnaire used in the Spanish ALADINO study [95]. It includes date of birth, sex, place of residence, sports experience, grade, date and time of measurement, clothes worn at the time of measurement, and name and address of the school.

Parents’ self-perceived physical fitness: using the International Fitness Scale (IFIS) questionnaire [96]. It has a Spanish version, and there are studies published in Chile that use it [97]. This questionnaire is composed of five Likert-type questions that describe the perception of general fitness, cardiorespiratory fitness, muscle strength, speed agility, and flexibility (Kappa = 0.45).

Parents’ Physical Activity Level: Global Physical Activity Questionnaire (GPAQ) designed by WHO. It incorporates information on physical activity participation and sedentary behavior in three settings: activity at work, activity while moving, activity during leisure time, and activity at work [98].

Cultural, social, and political context: School Questionnaire (Directors): Includes questions related to school physical activity policy, infrastructure, sports equipment, educational mission and vision, food received at school, and access to food during school hours.

Covariates: familial socioeconomic status, perception of environmental urban features parent’s and physical fitness parent’s.

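### The outcome model omits sex, is not linked to the covariates named in 2.7.2, and lets observed imbalance decide whether propensity scores are used

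*Protocol article*

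**What the plan says.** Four places in the protocol article bear on adjustment.

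- **Model (2.8.1).** Mixed regression is planned for each outcome, with treatment group as a fixed effect. The adjustment set is stated: "Models will be adjusted for baseline values, age, and classroom".
- **Covariate list (2.7.2, last line).** "Covariates: familial socioeconomic status, perception of environmental urban features", the latter as seen by the parents, and the parents' fitness. The sentence does not say which analysis these variables serve.
- **Sex.** It is recorded twice: in 2.7.1 ("In addition to sociodemographic variables (such as birth date and gender), the following information will be collected from each participant at baseline") and in the school questionnaire in 2.7.2 ("It includes date of birth, sex, place of residence, sports experience, grade"). It is in neither the model nor the covariate list.
- **Fallback (2.8.1).** The modelling follows a check that randomization worked. If imbalances threaten the comparability of the groups, "propensity scores will be utilized to control for covariate imbalances". No threshold, variable list or way of using the score is given, and the step is not labelled a sensitivity analysis.

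**The concern.** Sex is plausibly prognostic for body fat, running performance, jump and grip strength in adolescents. It is already recorded and costs one individual-level degree of freedom. The model instead carries age, which can vary little in a single school year (2.5: "All first-year high school students (approximately aged 15 to 16 years old").

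Two analysts could also read the article differently. One would fit the 2.8.1 terms only. The other would add the 2.7.2 covariates, or put them in a propensity score.

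Finally, under correct randomization any baseline difference is due to chance, so checking whether randomization worked answers no useful question. Here it can nevertheless change how the effect is estimated, after the groups have been compared. With only six classrooms, some visible imbalance is a realistic prospect.

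**Working it through.** **1. The plan's own figure.** Section 2.3 gives a difference of 3 points, SD 5, 30 students per cluster, variance inflation factor (VIF) 1.05, alpha 0.05 (two-sided assumed) and power 0.80. With g classrooms per arm and 2(g − 1) degrees of freedom, the number needed is 2 × SD² × VIF × (t₀.₉₇₅ + t₀.₈₀)² / (difference² × 30). At g = 3 (4 df) this is 2.69, which rounds up to the stated 3. The standard error is √(2 × 25 × 1.05 / 90) = 0.764 and noncentral-t power is 0.831. The sample size is not in dispute.

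**2. Side-by-side reading.** Model terms: baseline value, age, classroom. Covariates in 2.7.2: family socioeconomic status, parents' perception of the environment, parents' fitness. No variable is common to both, and sex is in neither.

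**3. Precision from adding sex, with baseline already in the model.** The documents give neither a sex gap D nor a baseline-to-follow-up correlation ρ, so these are assumptions: within-sex SD 5, equal numbers of boys and girls, the same gap at both visits.

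- Total variance V = 25 + D²/4; covariance of the two visits C = 25ρ + D²/4.
- Residual variance without sex = V − C²/V; with sex = 25(1 − ρ²).
- Example, D = 5 and ρ = 0.5: V = 31.25, C = 18.75; without sex 31.25 − 11.25 = 20.00; with sex 18.75. The SE ratio is √(18.75/20.00) = 0.968.

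| Sex gap | ρ = 0.5 | ρ = 0.7 | ρ = 0.9 |
|---|---|---|---|
| 5 | 0.968 | 0.983 | 0.995 |
| 8 | 0.941 | 0.967 | 0.990 |
| 10 | 0.926 | 0.959 | 0.987 |

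The SE therefore falls by about 0.5% to 7%. On the design variance of step 1, a partial R² for sex of 0.02, 0.05 or 0.10 moves power from 0.831 to 0.838, 0.848 or 0.866. The number of clusters does not change.

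**4. Chance sex imbalance.** With 90 per arm, half of them girls, and VIF 1.05, the SD of the between-arm difference in proportion female is √(0.25 × 2/90 × 1.05) = 0.076. A difference above 10 points has z = 0.10/0.076 = 1.31 and probability 0.19. A difference above 20 points has z = 2.62 and probability about 0.01.

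**5. Resulting shift.** If boys and girls differ by 1 to 2 points in change (assumption), a 10-point imbalance shifts the estimate by 0.10 × 1 to 0.10 × 2 = 0.1 to 0.2 points, or 3% to 7% of the planned 3 points. Step 3 assumes a constant gap instead, so it is a separate scenario. There the sex difference left after baseline adjustment is D(1 − C/V), which runs from 0.4 (D = 5, ρ = 0.9) to 2.5 (D = 10, ρ = 0.5). That is the same order of size.

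**6. How often the fallback might be triggered.** The article gives no rule. If imbalance were judged by independent tests at 0.05 (assumption), 1 − 0.95ᵏ gives 14%, 26% or 40% for 3, 6 or 10 covariates by chance alone.

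**The case against.** The strongest reply is that little is wrong here. A randomized comparison is valid without sex in the model, and baseline body fat already carries most of the sex effect. The 2.7.2 line may simply list variables collected for the propensity score. The propensity sentence follows those on sensitivity analysis and imputation and nowhere says it replaces the primary model. Thresholds and variable lists commonly belong in a full analysis plan. Age in the model does no harm.

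Much of this stands, and it rules out four stronger readings that a reader might infer.

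- **That the two lists contradict each other.** They do not overlap, but 2.7.2 never says its covariates enter the outcome model. The fault is an unstated link. The charitable reading is possible but not written down, and it would still make use of those covariates depend on the data.
- **That omitting sex biases the trial.** Chance imbalance is random error, not bias.
- **That a large share of variance is wasted.** Before baseline adjustment, sex gaps of 4 to 8 points would explain (D²/4)/(25 + D²/4) = 14% to 39% of the variance. The planned model does adjust for baseline. Likewise, a 20-point sex imbalance is a roughly 1% event on the assumptions of step 4. Stronger clustering of sex by class would make it likelier, but the article gives nothing on that.
- **That there are two primary results or an inflated error rate.** The article does not say so, and no inflation has been shown. The 14% to 40% figures assume tests the article does not specify.

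What the reply does not remove is that the article itself states one adjustment set, names another without a role, and makes a further method conditional on what the groups look like.

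**Conclusion.** The point holds as a worthwhile, low-cost improvement and clarification. It is not a flaw that invalidates the design. Three facts are plain from the text: sex is collected but unused, the 2.7.2 covariates have no stated role, and the propensity-score step depends on observed imbalance and is not labelled a sensitivity analysis.

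For body fat the numerical stake is probably modest: an SE reduction of about 0.5% to 7%, and a shift of about 0.1 to 0.2 points under a 10-point sex imbalance. These figures rest on assumed sex gaps, correlations and differences in change, none of which the documents supply. The within-sex SD of 5 is also an assumption. With gaps of 5 to 10 points it implies an overall SD of √31.25 = 5.6 to √50 = 7.1, against the planned 5. The case for fixing the adjustment set in advance does not depend on any of these numbers.

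**What to change.** 1. In 2.8.1, prespecify one model for every outcome: baseline value of that outcome, sex, age and school as fixed effects, with classroom as the random cluster effect. School belongs in the model because 2.4 places an experimental and a control group in each school.
2. In 2.7.2, state whether family socioeconomic status and the parental measures enter that model or are dropped. If kept, use baseline values only, since the batteries are given before and after the intervention.
3. Remove the check on randomization as a trigger, together with the propensity-score step. Alternatively, keep propensity scores only as a labelled sensitivity analysis with its variables and method named.

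**Cost.** Wording only: no new data, and one individual-level degree of freedom for sex. School is not free. With six classrooms, fitting a mean, treatment and two school terms leaves 6 − 1 − 1 − 2 = 2 between-classroom degrees of freedom, not the 4 that reproduce the planned size. On the design variance of 2.3, with no credit for baseline adjustment, noncentral-t power would be 0.55 against 0.83. The degrees-of-freedom method and the power under the final model should therefore be restated together.
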